### Objective

The main purpose of the present study is to build on the earlier pilot study with an improved design, in which we blindly assess the effects of individual music therapy delivered by an accredited music therapist on directly observed well-being and related outcomes such as NPS, agitation, depression, quality of life and pain controlled for individual attention in nursing home residents with dementia who also have NPS.

### Trial design

The design involves an individual randomized controlled trial (RCT) employing longitudinal repeated measurements in nursing home residents with dementia and NPS. The study is single blinded. The research assistant who assesses the primary outcome well-being and the secondary outcome pain through observation does not know whether residents participate in the experimental group or the control group. The music therapist and the patients themselves cannot be blinded to the condition they are assigned to. Nursing staff that performs the measurements as part of the secondary outcomes is not blinded either. The research takes place at eight nursing homes facilities of a health care organization in the Netherlands. Music therapy is provided in 30-minutes sessions, twice a week for 12 weeks, in their own room. The control group receives a ‘social’ visit with individual attention with the same frequency and of the same duration.

A process evaluation is performed according to an approach developed by Saunders [31], using components from Linnan and Steckler’s [32]. The process evaluation is based on mixed methods, collecting quantitative and qualitative data. Qualitative data collection comprises a focus group discussion with participants of health care professionals to evaluate barriers and facilitators influencing the implementation of research protocol. Quantitative data is gathered with questionnaires about reach, dose delivered, dose received, fidelity, recruitment and participant engagement. Quantitative data is gathered with questionnaires at 1, 2, 6 and 12 weeks after the baseline assessment completed by music therapists (intervention) or attendants (control). The questionnaires include items about participation in the sessions, fidelity, dose, engagement and about levels of implementation. Nurses and a research assistant will fill a questionnaire at the end of treatment to evaluate the process of implementation. Quantitative data will be analyzed with descriptive statistics.

## Methods

### Study setting

The study population consist of a sample of residents with dementia and NPS, residing on psychogeriatric units in one of eight nursing homes facilities of a health care organization (Amstelring) in the Netherlands.

### Participants’ eligibility

#### Inclusion criteria

First, potentially eligible participants of psychogeriatric units in eight nursing homes are screened for eligibility according to the following criteria:

Candidate has a charted diagnosis of dementia, which is in general according to Diagnostic and Statistical Manual of Mental Disorders IV criteria (American psychiatric association, 2001).Display a clinically relevant NPS measured with the Neuropsychiatric Inventory Nursing Home Version (NPI-NH) [33, 34] with the Frequency X Severity item score for at least one individual item rated 4 (Wood, 2000 [35]; Margallo, 2001 [36], Zuidema, 2007 [3], Zuidema, 2010 [37].

#### Exclusion criteria

Candidate having received individual music therapy before or having participated in a music therapy group in the past 3 months.Candidate has major comorbid psychiatric diagnosis (i.e., schizophrenia, psychosis, anxiety disorder). Due to an overlap between depression and dementia [38], candidate participants with a history of depression will not be excluded.Candidate has a hearing impairment that hampers the listening to music at a moderately volume. We use item 1a of the Severe Dual Sensory Loss in old age screening tool (SDSL) [39]. SDSL was found a valid and reliable tool [40].

### Demographic variables

Demographic variables such as age and gender will be assessed at baseline from the electronical medical chart review.

At baseline, nurses will register whether the resident has any background in music with questions about their experiences with music before entering the nursing home. The relatives of participants are asked closed-ended questions if the participant:

Has no experience with music in the past.Played an instrument before or was involved in singing activities or made music in some other way.Has served as a professional musician.

## Material and procedure

### Intervention

The participants of the intervention group (music therapy) receive 30 min of individual music therapy twice a week for 12 weeks in their own room. Music therapists use music experiences to promote health [41]. In this trial, music therapy consists of individual active music therapy sessions with also receptive techniques. Individual music therapy implies a one-to-one contact between the music therapist and the patient using a person-centered approach. Receptive and active music therapy are often combined [42]. Receptive therapeutic interventions consist of listening to music by the therapist who sings, plays, or selects recorded music for the recipients. In active music therapy, recipients are actively involved in the music-making, for instance by playing on small instruments. The participants may be encouraged to participate in musical improvisation with instruments or voices, movements activities or singing.

To determine the precise content of the intervention and to standardize procedures amongst all music therapists of Amstelring we conducted a focus group with 7 music therapists working at the nursing home facilities of Amstelring. We used a group interview because reaching a consensus is best achieved in a group setting. The focus group established a therapy protocol that comprised six steps for this study purpose:

All participating music therapists are employed by the nursing home organization. The music therapists are qualified and credentialed professionals by the federations for music therapy in the Netherlands (NVvMT), indicating that they have all been trained at an acknowledged and certified music therapy study program.The music therapist will ask, before the start, the participant or a legal representative about the musical preferences of the participant with a questionnaire (Gerdner, 2010 [43], Raven-de Vries, 2018 [44]). Based on this information, the music therapist will develop an individual music therapy session for the participants.Music therapists start each session trying to connect with the patient by eye contact, calling the name or giving a hand, to build trust.Music therapists use an observation list between 4 and 6 weeks. This observation list is based on the improvisational music therapy guideline of Kurstjens [45] and has been used to identify which important musical elements are of help in the approach of the problem.The music therapists will adapt the therapy continuously to needs and wishes of the participants. Participants receive an individual session tailored to the musical preferences of the participant.The participant will be invited to make a choice out of different musical instruments such as a guitar, keyboard, drums, maracas, etc. The therapist will aim at using active techniques mainly, for example improvisation where participants will try to play the instruments, sing together, clap the hands, move the body or face with the music. Also, receptive techniques will be used such as listening to live or pre-recorded music. The music therapist provides a safe environment, in which the participant can experience contact, interaction, atonement, structure and a natural finishing of the session.

In case of refusal of the session of adverse reactions such as fatigue or traumatic memory during the sessions, music therapists inform the researcher ([name]). The music therapists then stop immediately. Music therapists fill in questionnaires at 1, 2, 6 and 12 weeks after the intervention starts to gather information for the process evaluation. During the Covid-19 outbreak, the music therapists (intervention group) use gloves and face masks during the sessions.

### Control condition

The control group receives 30 min of individual attention twice a week for 12 weeks with no therapeutic basis. Individual attention will take place through a social visit, during which an attendant will drink coffee or tea with the participant. The individual attention will be given in the resident’s room by one attendant, who will have a conversation with the participant, drink coffee without an intervention goal such as cognitive training and without any musical intervention. The person who is doing the social visits is an informal care support company employee or volunteer. The attendants are students who work for an informal care support company and had a workshop about dementia. This is on top of the regular usual care delivered. The attendant starts every session by trying to connect with the patient via eye contact, calling his/her name or giving a hand, to build trust.

The attendants from the informal care support company or care support volunteer who provide the individual attention report attended sessions in the participants forms. In case of refusal of the session, the attendants inform the researcher ([name]). The individual attention will then stop immediately. Attendants fill in questionnaires at 1, 2, 6 and 12 weeks after the individual attention starts to gather information for the process evaluation. During the Covid-19 outbreak, the attendants (control group) use gloves and face masks through the sessions.

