**Physical activity**: rest-activity data will be collected by a MotionWatch (CamNtech Ltd, Cambridge, UK). The MotionWatch measures the arm movements of the participant; based on these movements, the rest-activity and physical activity are determined. It quantifies accelerations due to motor activity of the arm and integrates these over I-minute periods. The MotionWatch has the size and shape of a watch, is worn on the dominant wrist. The participants will be asked to wear the MotionWatch twenty-four hours a day for 1 week in the week before the intervention starts (T0) and the week directly after the last intervention session (T2). Nurses are asked to temporarily take off the MotionWatch when the participant takes a shower, performs another activity in which the MotionWatch could be exposed to too much water. Nurses will report the time that devices are taken off. Five parameters are calculated: Interdaily Stability (IS), Intradaily Variability (IV), Relative Amplitude (RA), most active period of 10 h and least active period of five hours. First, the IS variable that quantifies the strength of coupling between the rest-activity rhythm and supposedly stable Zeitgebers (e.g., meals) is calculated. IV, which quantifies the fragmentation of the rhythm, that is, the frequency and extent of transitions between rest and activity. RA quantifies the difference between the main activity (day) and rest (night) periods. The parameter of 10 most active hours (M10) is used to determine the amount of physical activity. The parameter (L5) are least active periods of five hours to determine rest activity.

Data on chronic psychotropic drug use will be derived from the electronic medical chart. Psychotropic drugs will be categorized into antipsychotics, anxiolytics, hypnotics, antidepressants and anti-dementia drugs according to the Anatomical Therapeutic Classification (ATC) system.

Any attrition or adverse effects of the interventions will be documented. The interventions will be discontinued if, in consultation with the physician or psychologists, harmful effects are observed and are expected to continue with exposure to any of the two interventions.

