#### Study monitoring

This clinical trial does not involve a high-risk intervention. We do not expect adverse events or significant unintended effects of the intervention. However, the participants of this study are vulnerable subjects and monitoring, and quality assurance will be necessary according to national legislation (WMO). The Department of anesthesiology (an independent department of UMCG) will be responsible for the data monitoring.

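### Adverse reactions are named in the session-reporting instruction for music therapists but not for control attendants, although the article promises documentation of harms from both interventions

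*Protocol article*

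**What the plan says.** Four places in the protocol article bear on this point.

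- **Intervention:** "In case of refusal of the session of adverse reactions such as fatigue or traumatic memory during the sessions, music therapists inform the researcher". The second "of" reads as a slip for "or", so the triggers are refusal and adverse reactions.
- **Control condition:** "In case of refusal of the session, the attendants inform the researcher". Adverse reactions are not mentioned. The attendants also "report attended sessions in the participants forms".
- **Trial design:** both arms complete process-evaluation questionnaires at 1, 2, 6 and 12 weeks. On their content: "The questionnaires include items about participation in the sessions, fidelity, dose, engagement and about levels of implementation".
- **Secondary outcomes measures:** "Any attrition or adverse effects of the interventions will be documented". The next sentence provides for discontinuation, after consultation with the physician or psychologists, where "harmful effects are observed and are expected to continue with exposure to any of the two interventions".

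**The concern.** The paragraphs on the two arms are built alike: the same opening of each session, the same report to the researcher, the same questionnaire schedule, the same mask and glove provision. The trigger for a report is one of the few things that differ. The control visit takes place in the resident's own room with one attendant, who is the main witness to anything that happens during it. As published, the article gives that person no adverse-reaction instruction to match the one given to the therapist.

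What is at stake is any statement about harms by arm. The control condition exists to separate music therapy from individual attention. If fatigue or distress is noted more completely in one arm, a difference in recorded reactions could come from reporting and not from the treatment. The article itself says that residents with severe dementia cannot always report on their own state, so a reaction that the attendant does not pass on may never reach the record.

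**Working it through.** No figure in the article can be reproduced here, because the point concerns instructions. The check sets the passages side by side.

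**1. Opportunity to observe a reaction.** Under Trial design, "The control group receives a ‘social’ visit with individual attention with the same frequency and of the same duration". Both arms are planned at 30 minutes, twice a week, for 12 weeks: 2 × 12 = 24 sessions, and 24 × 30 = 720 minutes (12 hours) per resident. By design the opportunity is equal.

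**2. Who reports, and on what trigger.**

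| | Music therapy | Control |
|---|---|---|
| Reporter | Credentialed music therapist, unblinded | Student or volunteer attendant, necessarily aware of the condition |
| Refusal reported to researcher | Yes | Yes |
| Adverse reaction reported to researcher | Yes, with two examples | Not mentioned |
| Process questionnaires | Weeks 1, 2, 6, 12 | Weeks 1, 2, 6, 12 |
| Adverse reactions among listed questionnaire items | No | No |

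**3. Whether another stated route closes the gap.** The attendants' participant forms are described as recording attendance. The listed questionnaire topics do not include adverse reactions. The blinded research assistant observes residents only at the baseline, week 6 and week 12 assessments, so does not follow most sessions. The trial-wide sentence under Secondary outcomes measures does cover the control arm, but it does not say who reports a control-arm reaction or how it reaches the record.

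**4. Size.** The article gives no reaction rate and no capture rate. In general, suppose the true risk is the same in both arms and control reactions are recorded with completeness c relative to the music therapy arm. The apparent risk ratio, music therapy versus control, is then

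1 / c.

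Taking c purely as an assumption:

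- c = 1 (trial-wide provision fully applied): 1 / 1 = 1.0
- c = 0.75: 1 / 0.75 = 1.33
- c = 0.5: 1 / 0.5 = 2.0

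The article does not fix c. These values show the direction and form of the effect; they do not estimate it.

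**The case against.** The strongest reply is that the trial-wide provision already covers both arms. It promises documentation of adverse effects without exception, and the discontinuation sentence names either intervention as a possible source of harm. On that view the control paragraph merely fails to repeat a general duty, and the wording of forms is operational detail that a journal article leaves to the full protocol.

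Part of this stands. A reader might infer that attendants report refusals and nothing else, or that harms are in fact counted unequally. The article supports neither: it does not restrict attendants to refusals, and the full content of the forms and questionnaires is not shown. The reply does not dispose of the point, however. The article is not simply silent. It states an instruction for each arm, the two differ, and the control version does not match the general promise. If the full protocol resolves this, the published text should agree with it.

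It is also fair to say that harms are not among the listed secondary outcomes, do not appear in Table 1 and are not mentioned under Data analysis. The consequence is therefore limited to whatever description of harms by arm is eventually given.

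Two further inferences are tempting and should not be drawn. One is that the analysis of missing data is affected: no stated analysis uses reasons for stopping, attrition is to be documented without distinction of arm, and both arms report refusals. The other is that the sentence under Study monitoring, "We do not expect adverse events or significant unintended effects of the intervention", contradicts the therapists' instruction. An instruction for what to do if a reaction occurs is a contingency, and it is compatible with not expecting one.

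**Conclusion.** The point holds as a mismatch between the two session-level reporting instructions and the trial-wide provision on harms. Control-arm reactions may be under-ascertained, and the likely direction is against music therapy. Whether an imbalance arises, and how large it would be, cannot be established from the article.

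The conclusion rests on two assumptions: that the therapists' sentence is meant to cover adverse reactions as well as refusals, and that staff follow the instructions as published. The blinded DS-DAT outcome and the sample size do not depend on these reports and are unaffected. The point is modest in reach. It deserves correction because the participants are vulnerable and the remedy is nearly free.

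**What to change.** Reconcile the Intervention, Control condition and Secondary outcomes measures sections so that one identical adverse-reaction reporting instruction applies to music therapists and attendants, with the same prompt on the session form in both arms. Report adverse reactions by arm. If sessions have already been delivered under differing instructions, say so when harms are reported, so that readers can weigh any difference between the arms accordingly.

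The change should be confined to reporting. In both sections the reporting sentence is followed by wording on when sessions stop, so carrying the therapists' sentence over whole would also alter when control visits stop. That stopping wording is for the sponsor to reconcile, and no rule is proposed here.

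The cost is one sentence in the text and one line on a form that attendants already complete, with no extra staff.

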### Primary outcome measure

Observed well-being is the primary outcome measure rather than multidimensional quality of life with proxy estimation of domain ratings based on recall. Lawton has most extensively explored the concept of QoL concerning dementia and described QoL in dementia in terms of four sectors: psychological well-being, behavioral competence, objective environment (response to surroundings) and perceived QoL [46–48]. Jonker et al. reviewed conceptual developments in QoL research concerning dementia and based on the dimensions presented by Lawton, they identified psychological well-being as the core dimension of QoL of patients with dementia. Patients with severe dementia cannot always self-report their psychological well-being [49] but indicators of wellbeing of persons with dementia can be observed with validated instruments. We assess well-being with an objective observational instrument−the Discomfort Scale - Dementia of Alzheimer Type (DS-DAT) where discomfort is defined as a negative emotional and/or physical state subject to variation in magnitude in response to internal or environmental conditions. It is a scale for direct observation of behavior of a patient and is applicable also in later phases of dementia [50]. The Dutch translation is characterized by a good reliability (Hoogendoorn. 2001) [51] and validity (van der Steen, 2002) [52, 53]. The scale consists of 9 items measuring 7 negative and 2 positive items regarding vocalization, breathing, facial expression, and body movements. The nine 4-point items are summed for a total score ranging from 0 (no observed discomfort) to 27 (highest possible level of observed discomfort). Well-being will be assessed by a blinded research assistant at baseline (T0), six weeks (T1) and twelve weeks (T2). Well-being is assessed during 5 min before and after the music therapy sessions or individual attention sessions. The research assistant will be trained in using the DS-DAT trough an instructional video and practice completion of the DS-DAT with videotaped patients. Feedback is provided against the scores of the scale’s developer ([name]) who had rated the patient video clips.

### Secondary outcomes measures

Secondary outcomes are also assessed in all /participating residents and include pain, quality of life, neuropsychiatric symptoms (agitation, anxiety, symptoms of depression), quality of sleep and psychotropic drug use.

**Pain** will be assessed by a blinded research assistant at baseline, six weeks and twelve weeks during 2 min before and after the intervention session or individual attention with the PAIC-15 (Pain Assessment in Impaired Cognition) [54, 55] which is an observational assessment instrument that lists 15 items and uses scores from 0 to 3 for each item. PAIC-15 comprises three domains: facial expression, body movements and verbalizations/vocalizations. Each domain has 5 items and the total score is the sum of all items, ranging from 0 to 45. The research assistant will be trained in using the PAIC-15.

**Quality of life** will be rated by non-blinded nurses at baseline (T0), at six weeks (T1) and at twelve weeks (T2) with the Quality of Life in Late-Stage Dementia Scale (QUALID) [56] that can be used with late-stage dementia patients in institutional settings and has been designed for proxy-rating by nurses. Responses reflect patient behavior over the past seven days. The QUALID consists of eleven items that are short and simple and is characterized by a good reliability and validity and the Dutch translation was a valid measure for quality of life in patients with advanced dementia [57]. The total score is the sum of all items, ranging from 11 to 55. Lower scores indicate a higher quality of life.

**Neuropsychiatric symptoms (NPS)** will be assessed by non-blinded nurses at baseline (T0), at six weeks (T1) and at twelve weeks (T2) with the Neuropsychiatric Inventory Nursing Home Version (NPI-NH), a scale originally developed by Cummings [33, 34] to assess NPS in outpatients with dementia. The nursing home version was developed for use of professional caregivers in institutions and proved to be valid and reliable for trained nursing staff [58, 59]. The NPI-NH is the only nursing home instrument to assess NPS that occurred in the past four weeks that has been translated into Dutch [60]. The NPI is a structured interview that includes 12 neuropsychiatric symptoms: delusions, hallucinations, agitation, depression, anxiety, euphoria, apathy, disinhibition, irritability, aberrant motor behavior, night-time disturbances and appetite/eating change. Frequency (F) and severity (S) of each symptom are rated on a four (1–4) and three (1–3) point scale respectively. A separate score can be calculated for each symptom by multiplying the frequency and severity (FxS score), resulting values range from zero to 12 for each symptom. Summing all FxS scores results in a total score that ranges from 0 to 144. Interview also includes a caregiver distress questions using a 5-point scale.

**Agitation and aggression** will be assessed by non-blinded nurses at baseline (T0), 6 weeks (T1) and 12 weeks (T2) using the caregiver rated questionnaire Cohen-Mansfield Agitation Inventory (CMAI). This instrument, developed by Cohen-Mansfield and Billig [61] and validated by Miller [62] is an instrument that specifically addresses agitation or aggression that has been translated into Dutch. The Dutch translation of the CMAI (CMAI-D) has been validated by De Jonghe [63] and rated agitated behaviors occurred during last two weeks. The frequency of each symptom is rated on a seven-point scale (1–7) ranging from ‘never’ to ‘several times an hour’. Summing all symptom scores results in a total score that ranges from 29 to 203.

**Depression** will be rated by non-blinded nurses at baseline (T0), at six weeks (T1) and twelve weeks (T2) with the Cornell Scale for Depression in Dementia (CSDD) [64], which has good internal consistency [65]. Responses reflect symptoms of depression in the week before. The CSDD is a 19-item instrument, with scores for each item ranging from 0 to 2 (total score range 0–38). The CSDD has been translated into Dutch [66].

**Physical activity**: rest-activity data will be collected by a MotionWatch (CamNtech Ltd, Cambridge, UK). The MotionWatch measures the arm movements of the participant; based on these movements, the rest-activity and physical activity are determined. It quantifies accelerations due to motor activity of the arm and integrates these over I-minute periods. The MotionWatch has the size and shape of a watch, is worn on the dominant wrist. The participants will be asked to wear the MotionWatch twenty-four hours a day for 1 week in the week before the intervention starts (T0) and the week directly after the last intervention session (T2). Nurses are asked to temporarily take off the MotionWatch when the participant takes a shower, performs another activity in which the MotionWatch could be exposed to too much water. Nurses will report the time that devices are taken off. Five parameters are calculated: Interdaily Stability (IS), Intradaily Variability (IV), Relative Amplitude (RA), most active period of 10 h and least active period of five hours. First, the IS variable that quantifies the strength of coupling between the rest-activity rhythm and supposedly stable Zeitgebers (e.g., meals) is calculated. IV, which quantifies the fragmentation of the rhythm, that is, the frequency and extent of transitions between rest and activity. RA quantifies the difference between the main activity (day) and rest (night) periods. The parameter of 10 most active hours (M10) is used to determine the amount of physical activity. The parameter (L5) are least active periods of five hours to determine rest activity.

Data on chronic psychotropic drug use will be derived from the electronic medical chart. Psychotropic drugs will be categorized into antipsychotics, anxiolytics, hypnotics, antidepressants and anti-dementia drugs according to the Anatomical Therapeutic Classification (ATC) system.

Any attrition or adverse effects of the interventions will be documented. The interventions will be discontinued if, in consultation with the physician or psychologists, harmful effects are observed and are expected to continue with exposure to any of the two interventions.

The nurses will determine the stage of dementia, measured with the Global Deterioration Scale (GDS) [67, 68] at baseline. The DS describes seven stages: ‘no global impairment’ (1), ‘very mild cognitive decline’ (2), ‘mild cognitive decline’ (3), ‘moderate cognitive decline’ (4), ‘moderately severe’ (5), ‘severe’ (6) and ‘very severe global impairment’ (7).

